## Abstract

**Background:**

The International Liaison Committee on Resuscitation (ILCOR) now recommends therapeutic hypothermia (TH) (33°C for 12-24 hours) as soon as possible for patients who remain comatose after resuscitation from shockable rhythm in out-of-hospital cardiac arrest and that it be considered for non shockable rhythms. The optimal timing of TH is still uncertain. Laboratory data have suggested that there is significantly decreased neurological injury if cooling is initiated during CPR. In addition, peri-arrest cooling may increase the rate of successful defibrillation. This study aims to determine whether paramedic cooling during CPR improves outcome compared standard treatment in patients who are being resuscitated from out-of-hospital cardiac arrest.

**Methods/Design:**

This paper describes the methodology for a definitive multi-centre, randomised, controlled trial of paramedic cooling during CPR compared with standard treatment. Paramedic cooling during CPR will be achieved using a rapid infusion of large volume (20-40 mL/kg to a maximum of 2 litres) ice-cold (4°C) normal saline.

The primary outcome measure is survival at hospital discharge. Secondary outcome measures are rates of return of spontaneous circulation, rate of survival to hospital admission, temperature on arrival at hospital, and 12 month quality of life of survivors.

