### Sample Size

This study consists of two parallel clinical trials, separately testing the effect of paramedic cooling during CPR in patients with a shockable rhythm (VF/VT) and non-shockable rhythm (asystole/pulseless electrical activity).

The primary outcome measure for post-VF arrest patients is survival at hospital discharge. Data from the Victorian Cardiac Arrest Register shows that patients who are in ventricular fibrillation on arrival of paramedics have a 40% rate of return of spontaneous circulation, and there was a 50% subsequent survival rate in the previous Melbourne cooling trial [16]. The overall current survival rate based on all participating states is circa 20%. We propose that a rapid infusion of cold IV fluid will increase the rate of return of spontaneous circulation based on laboratory data cited above from 40% to 45%, and that this very early cooling will increase the overall survival rate from 20% to 27%. With 80% power and a type 1 error of 0.05, the study requires a sample size of 603 post VF-arrest patients in each arm (1206 in total).

Randomization of patients with non-VF will occur concurrently. The primary outcome measure for non-VF/VT cardiac arrest patients is also survival at hospital discharge. Currently, the outcome at hospital discharge of these patients is 2% [3]. To demonstrate improved outcomes to 5% (an absolute difference of 3%) requires 653 per group, a total of 1306 patients.

For both studies, secondary outcome measures are the rates of return of spontaneous circulation [23], survival to hospital admission on all patients, and quality of life measured by telephone follow up at 12 months using the Glasgow Outcome Scale Extended (GOSE) [24], EQ-5D [25] and SF-12 Health Survey Summary Score [26]. Analysis will be based on "Intention-to-treat".

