### Data Collection

All data relevant to the study is currently recorded by paramedics immediately after the case as a Patient Care Record. Furthermore, Victoria, Western Australia and South Australia each have a cardiac arrest registry that records the patient, event and outcome data consistent with the Utstein criteria [23] for all OHCAs attended. The Victorian Cardiac Arrest Registry currently conducts a 12-month quality of life follow-up on all survivors. Victorian survivors will therefore be contacted 12 months post cardiac arrest to complete a functional and quality of life outcomes telephone questionnaire.

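### The 12-month quality-of-life outcome is defined in survivors only, so an arm comparison on it is not protected by randomisation and could mislead

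*Protocol article*

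**What the plan says.** The Abstract (Methods/Design) of the protocol article states: "The primary outcome measure is survival at hospital discharge". It then lists the secondary outcomes, the last being "12 month quality of life of survivors".

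Sample Size repeats the outcome for both parallel trials as "quality of life measured by telephone follow up at 12 months using the Glasgow Outcome Scale Extended (GOSE"), together with EQ-5D and SF-12. In the same sentence, the reference to all patients is attached to survival to admission and not to quality of life. The next sentence says that analysis will follow intention-to-treat.

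Data Collection says that the Victorian registry "currently conducts a 12-month quality of life follow-up on all survivors" and concludes: "Victorian survivors will therefore be contacted 12 months post cardiac arrest". It mentions no equivalent follow-up in Western Australia or South Australia.

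Sample Size also gives the survival effect that the trial is built on. In VF, cooling is expected to "increase the overall survival rate from 20% to 27" per cent. In non-VF, the assumed change is from 2% to 5%.

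No section assigns a score to patients who die before 12 months, combines death with function, or calls the quality-of-life comparison descriptive.

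**The concern.** Being alive at 12 months is determined after randomisation, and survival is what the treatment is intended to alter. If cooling works as planned, the cooled survivors are a mixture: patients who would have lived in either arm, and patients who live only because they were cooled. The control survivors contain only the first kind. A difference in mean GOSE, EQ-5D or SF-12 between these groups mixes any effect on function with a change in who is left to be measured.

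If the extra survivors have poorer function, the cooled mean falls although no patient was harmed. If they do as well as the others, nothing shifts. If cooling instead removed frail survivors, the cooled mean would rise. A reader of the trial report could not tell these cases apart from survivor means alone. Of the outcomes listed, the 12-month instruments are the only ones that measure function, so a misleading result here has nothing beside it to correct it.

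**Working it through.** **1. Is the survival effect the trial's own?** The stated sample sizes were reproduced with the two-sided two-proportion formula, alpha 0.05, 80% power, with continuity correction:
- VF, 20% v 27%: 603 per arm (575 without the correction). Stated: 603.
- Non-VF, 2% v 5%: 653 per arm (588 without the correction). Stated: 653.

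Both match, so these survival rates are the design assumptions and can be carried forward.

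**2. Who would be left out.** A comparison of survivors omits 1 - 0.20 = 80% of control and 1 - 0.27 = 73% of cooled VF patients. In non-VF it omits 98% and 95%.

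**3. Survivors without a counterpart.** Assume that cooling costs no lives and that discharge survival stands in for 12-month survival, which the article does not give. The share of cooled survivors alive only because of cooling is (pT - pC)/pT:
- VF: (0.27 - 0.20)/0.27 = 7/27 = 26%
- Non-VF: (0.05 - 0.02)/0.05 = 3/5 = 60%

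At full enrolment, discharge survivors in all three states would number about 603 × 0.20 = 121 v 603 × 0.27 = 163 (VF) and 653 × 0.02 = 13 v 653 × 0.05 = 33 (non-VF). If only Victoria is followed up, fewer will have quality-of-life data.

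**4. Effect on the comparison.** Utilities are not in the article and are assumed here: 0.80 for patients who survive in either arm, and *u* for the extra survivors, with *u* from 0.80 down to 0.30. No patient is harmed in any scenario.
- Survivor-only difference (cooled minus control) = -[(pT - pC)/pT] × (0.80 - *u*)
- All-patient difference with death = 0: pT × (cooled survivor mean) - pC × 0.80 = (pT - pC) × *u*

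| *u* | VF survivors only | VF all patients | Non-VF survivors only | Non-VF all patients |
|---|---|---|---|---|
| 0.80 | 0 | +0.056 | 0 | +0.024 |
| 0.70 | -0.026 | +0.049 | -0.06 | +0.021 |
| 0.60 | -0.052 | +0.042 | -0.12 | +0.018 |
| 0.50 | -0.078 | +0.035 | -0.18 | +0.015 |
| 0.30 | -0.130 | +0.021 | -0.30 | +0.009 |

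Worked example, VF with *u* = 0.60: the cooled survivor mean is (0.20 × 0.80 + 0.07 × 0.60)/0.27 = 0.748, against 0.80 in control. Over all patients the means are 0.27 × 0.748 = 0.202 and 0.20 × 0.80 = 0.160, a difference of +0.042.

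The two comparisons have opposite signs whenever *u* is below 0.80. At *u* = 0.80 the survivor-only difference is zero.

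**The case against.** The strongest reply is that the article never states a survivor-only test between arms. It names an outcome in the Abstract, names instruments in Sample Size, and says in Data Collection who will be telephoned, and only survivors can be telephoned. How deaths enter a functional scale is usually settled in an analysis plan, which is not shown. This stands in part: no test or model is given, and a later plan could add a rule for deaths. But the restriction to survivors is in the outcome definition itself, for a randomised trial, with nothing marking it as descriptive. A plan that follows the definition inherits the problem.

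Several stronger readings are tempting, and the documents do not support them:
- *The outcome flatly contradicts intention-to-treat.* Reporting survivors by assigned arm is one loose use of that term, and the sentence could even be read as supporting an all-patient analysis. The fit is poor, but a contradiction is an inference.
- *The quality-of-life result carries the neuroprotection claim.* No section gives it that role. The Discussion frames the question as survival.
- *Cooling will appear harmful.* That requires the extra survivors to be worse off than the others, and nothing in the article says they will be.
- *All survivors counted in the working will have quality-of-life data.* Data Collection names only Victorian survivors.

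It is also fair to say that scoring death as zero makes the all-patient difference largely a restatement of survival. In the example, +0.042 is simply 0.07 × 0.60. This stands and is a real limit of the remedy, above all in non-VF, where 95% to 98% of patients would be scored as dead.

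**Conclusion.** The point holds for a secondary outcome and should be corrected. As defined, the 12-month comparison would be made between groups selected by the outcome that cooling is meant to change. The 26% and 60% shares follow from the article's own survival rates, given the two assumptions in step 3. The possible distortion, down to -0.13 in VF and -0.30 in non-VF against an all-patient benefit of at least +0.021 and +0.009, rests on the assumed utility range and shows what could happen, not what to expect. Follow-up confined to Victoria would shrink the numbers but would not remove the selection. The analysis of survival at hospital discharge is not affected.

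**What to change.** Restate the 12-month outcome so that any between-arm comparison includes all patients randomised where 12-month follow-up is run, which by Data Collection is Victoria. Randomisation is stratified by state, so that subset remains a randomised comparison.
- Analyse GOSE as an ordinal scale with death as the lowest category, or as favourable yes/no with death counted as unfavourable.
- Analyse EQ-5D utility with death = 0 as supportive.
- Report GOSE, EQ-5D and SF-12 in survivors beside 12-month survival in each arm, as description, with no treatment-effect claim.
- Treat survivors who are not reached or who object as missing, not as dead.

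The change is to the outcome and analysis wording. The state registries already record outcome data; that vital status at 12 months is among them should be confirmed. The price is that the all-patient scores are driven largely by mortality, most of all in non-VF, and so say little about function on their own. Showing the descriptive survivor scores next to them is the answer to that.

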**Discussion:**

This trial will test the effect of the administration of ice cold saline during CPR on survival outcomes. If this simple treatment is found to improve outcomes, it will have generalisability to prehospital services globally.

**Trial Registration:**

ClinicalTrials.gov: NCT01172678

## Background

Cardiovascular disease is a leading cause of premature death in Australia [1]. More than half of these deaths (approximately 25,000 per year) occur prior to hospital arrival. Despite sophisticated emergency medical service responses to sudden cardiac arrest, less than half of sudden cardiac arrest patients are able to be resuscitated by paramedics [2]. For those who are initially resuscitated and transported to hospital, the prognosis is still poor, particularly in rural areas [3]. Much of the mortality and morbidity after hospital admission is due to the anoxic brain injury sustained during the cardiac arrest [4].

One major recent advance in the treatment of severe anoxic brain injury following out-of-hospital cardiac arrest is therapeutic hypothermia (TH). When induced after resuscitation, this treatment was shown to improve neurological and overall outcomes in two randomized, controlled clinical trials [5,6]. The International Liaison Committee on Resuscitation (ILCOR) now recommends TH (33°C for 12-24 hours) as soon as possible for patients who remain comatose after resuscitation from out-of-hospital cardiac arrest for shockable rhythms and suggests that this therapy be considered for non shockable rhythms and in-hospital arrests [7,8].

The optimal timing of TH is still uncertain. Laboratory data have suggested that there is significantly decreased neurological injury if cooling is initiated during CPR [9-11]. Clinical and laboratory trials over the last three years have established that a rapid intravenous infusion of a large volume (20-40 mL/kg) of ice-cold fluid (i.e. normal saline) during CPR is a feasible and an effective method of induction of mild TH [12]. This technique has become widely used as a cooling method in the pre-hospital setting [13], the Emergency Department [14] and the Intensive Care Unit [15].

Previously, a randomised, controlled trial comparing paramedic cooling after return of spontaneous circulation (ROSC) with cooling in the emergency department was conducted in Melbourne. The study was stopped at the interim analysis due to a lack of difference in the primary outcome measure (outcome at hospital discharge) between the two groups [16]. Analysis of the data revealed that paramedics infused an average of 1000 mL ambient temperature saline during CPR prior to return of a spontaneous circulation as part of standard paramedic treatment and that cooling began approximately 30 minutes after paramedic arrival and only just prior to hospital cooling. Although there was a decrease in the core temperatures of the patients on arrival at the ED, this was a transient effect lasting only approximately 20 minutes. Subsequently, the cooling curves of the patients in both groups were identical. Thus, it was considered unlikely that this transient difference in core temperature could have a measurable effect on outcomes.

Further laboratory [17,18] and clinical research [19,20] has suggested that paramedic cooling during CPR is feasible and should be tested in large clinical trials. Boddicker et al [17] examined the success rates of defibrillation in swine cooled to different temperatures and found first-shock defibrillation success was highest in the hypothermia (33°C) group suggesting mild hypothermia may have a beneficial anti-arrhythmic effect, as well as a neuroprotective effect. Kämäräinen et al [20] cooled adult patients with out-of-hospital cardiac arrest during CPR and concluded that induction of therapeutic hypothermia during pre-hospital CPR was easily carried out and well tolerated. A study specifically examining respiratory function in patients treated with large volume, ice cold saline has indicated that there is no adverse effect on respiratory function [21] Garrett et al [22] in a retrospective analysis of a change in their prehospital cardiac arrest treatment protocols allowing intra-arrest induction of therapeutic hypothermia with 2000 ml of 4°C normal saline directly after obtaining IV/IO access concluded that TH during the intra-arrest period may improve the frequency of return of spontaneous circulation even at fluid volumes unlikely to change core body temperature.

Given these supportive laboratory and preliminary clinical data, we are conducting a definitive multi-centre, randomised, controlled trial of paramedic cooling during CPR compared with usual paramedic practice. We aim to determine whether paramedic cooling during CPR using a rapid infusion of large volume (20-40 mL/kg) ice-cold (4°C) normal saline improves outcome compared with standard treatment in patients who are being resuscitated from out-of-hospital cardiac arrest.

## Methods/Design

The RINSE trial is a prospective, multi-centre, randomised, single blinded, controlled trial conducted by the ambulance services of Victoria, Western Australia and South Australia.

In the treatment arm, paramedics will undertake immediate cooling on arrival and during cardiac arrest, using a large volume (20 mL/kg up to 2 litres) intravenous bolus of ice-cold saline. The saline infusion will be continued after return of circulation and en-route to hospital. In the control arm, patients will receive standard paramedic care, which includes the administration of normal saline at ambient temperature and will be cooled after arrival at the hospital (the current standard of care in ambulances in Australasia).

### Study sites

This is a three-centre funded study administered centrally through the Monash University Department of Epidemiology and Preventive Medicine with study sites in Victoria (Victoria Ambulance and Monash University); South Australia (South Australia Ambulance Service and Flinders University) and Western Australia (St John Ambulance and University of Western Australia). In Victoria, only MICA paramedics will enroll patients whereas in WA and SA all paramedics (but not transport officers) will recruit patients.

### Inclusion/Exclusion Criteria

Paramedics will screen patients during cardiac arrest and determine eligibility for enrolment. Adults 18 years and over, in cardiac arrest on arrival of paramedics are eligible for inclusion. Patients who are in cardiac arrest following trauma, or who are obviously pregnant or who are already hypothermic (tympanic temperature < 34.5°C) will be excluded.

### Randomisation

The ambulances will be provided with a set of randomisation envelopes. Block randomization will be used with instructions for immediate cooling therapy during CPR or instructions for standard treatment. Standard treatment includes cooling commenced at hospital as per ILCOR recommendations [7,8]. The envelopes will be randomised by computer-generated code into blocks of ten, numbered externally, and then sealed within an opaque envelope that conceals the treatment designation. All vehicles will carry two envelopes and as each is used, it will be replaced at the earliest convenient time from the remaining envelopes held at the ambulance station. Randomisation will be stratified by state to control for possible differences in paramedics skills and hospital treatment.

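### One fixed, published block size of ten, with envelopes held by the recruiting crews, makes allocations partly predictable where a station tracks their use; concealment itself is not broken

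*Protocol article*

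**What the plan says.** The Randomisation section fixes a single block size: "The envelopes will be randomised by computer-generated code into blocks of ten, numbered externally". The same sentence gives the safeguard, which is that each allocation is "sealed within an opaque envelope that conceals the treatment designation". On custody it says "All vehicles will carry two envelopes and as each is used, it will be replaced at the earliest convenient time", with replacements taken "from the remaining envelopes held at the ambulance station". The only stratification factor is state: "Randomisation will be stratified by state to control for possible differences in paramedics skills and hospital treatment".

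Under Inclusion/Exclusion Criteria, the recruiting decision lies with the crew: "Paramedics will screen patients during cardiac arrest and determine eligibility for enrolment". Study Treatments has the same crews give either ice-cold or standard-temperature saline. Methods/Design calls the study a "prospective, multi-centre, randomised, single blinded, controlled trial" and does not say who is blinded. That the crew knows the arm once the envelope is open is an inference, but a safe one.

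The Sample Size section states that analysis is by intention-to-treat. The article does not state an opening order within a vehicle, how opened or unused envelopes are accounted for, or whether a block stays at one station.

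**The concern.** Three features combine. The block size is constant and in print. The allocations are in local custody rather than released by a third party after enrolment. The people who hold them also decide who is eligible and see every allocation they deliver. In a balanced block of known size, each allocation seen shifts the odds on those that remain, and a sealed opaque envelope cannot prevent that.

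If a crew or station acted on such a guess, for instance by enrolling or not enrolling according to perceived prognosis, the arms would differ at baseline and survival at discharge would be biased. The differences sought are 7 percentage points (20% to 27%, VF) and 3 percentage points (2% to 5%, non-VF). The non-VF comparison rests on few events, so it is the more exposed.

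**Working it through.** **Inputs.** Block size 10 (Randomisation). Equal arms, 603 per arm in VF and 653 in non-VF (Sample Size). A 5:5 split in each block is an assumption drawn from the equal arms. Survival is 20% v 27% (VF) and 2% v 5% (non-VF), with 80% power and type 1 error 0.05 (Sample Size).

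**The plan's own figures.** The two-proportion formula, two-sided with continuity correction, gives 603 and 653 per arm, both exactly as stated. Without the correction it gives 575 and 588. The sample sizes are sound, and nothing below changes them.

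**Predictability of the next envelope.** Suppose k envelopes of a block have been seen, j of them from one arm. The numbers left are a = 5 - j and b = 5 - (k - j). The best guess names the arm with more left and is right with probability max(a, b)/(a + b). The chance of each j is C(5, j) × C(5, k - j)/C(10, k). Averaging over j gives:

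| Envelopes of the block seen | Best guess right | Next allocation certain |
|---|---|---|
| 0 | 50% | 0 |
| 1 or 2 | 55.6% | 0 |
| 3 or 4 | 59.5% | 0 |
| 5 | 64.3% | 0.8% |
| 6 | 64.3% | 4.8% |
| 7 | 72.2% | 16.7% |
| 8 | 72.2% | 44.4% |
| 9 | 100% | 100% |

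An example for k = 1: four of that arm and five of the other remain, so the guess is right 5/9 = 55.6% of the time.

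**Whole block tracked.** Summing the middle column over k = 0 to 9:

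0.500 + 2(0.5556) + 2(0.5952) + 2(0.6429) + 2(0.7222) + 1 = 6.53 of 10, or 65.3%.

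Summing the last column:

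0.008 + 0.048 + 0.167 + 0.444 + 1 = 1.67 of 10, or 16.7%.

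**Effect of block size.** The same calculation for a fixed, known size gives 70.8% for blocks of 4, 68.3% for 6, 65.3% for 10 and 61.7% for 20. Shrinking a known block makes prediction easier, so the remedy has to be variation and non-disclosure.

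**The second envelope.** If both carried envelopes come from one fresh block:

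- they hold different arms with probability 5/9 = 55.6%;
- at least one holds a given preferred arm with probability 1 - (5/10)(4/9) = 77.8%, against 50% if only the first may be used.

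That gain exists only for a crew that opens one envelope and puts it aside. Picking between two unopened envelopes leaves the chance of either arm unchanged.

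**How sensitive the non-VF result is.** Expected survivors are 0.02 × 653 = 13 and 0.05 × 653 = 33. Two-sided Fisher tests give:

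- 13 v 33: p = 0.004. Moving four survivors between arms, to 17 v 29: p = 0.098.
- With no effect, 13 v 13. Moving six, to 7 v 19: p = 0.027.

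This shows how few events carry the result. It does not show that such shifts will occur.

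**The case against.** A reader might infer that concealment has failed, that crews can generally guess the next arm, or that they may choose between two allocations. The documents support none of these.

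- **The safeguard is real.** Envelopes are sealed, opaque and numbered. Getting any use from the second envelope takes a breach of procedure, and any envelope system is open to that. This stands.
- **One crew sees little of a block.** Vehicles hold two envelopes and draw replacements from a station pool. If envelopes are handed out consecutively (an assumption), one block of ten could be spread over five vehicles. A crew that has seen none to two of a block is right 50-56% of the time, and certainty is impossible before five are seen. The 65% and 17% figures need an observer who follows the whole block. The article does not say that blocks stay at one station or that crews are told the size. This stands and limits the size of the point.
- **Rules on order and logging may exist.** The article condenses a fuller protocol that is not shown, so their absence here is no defect. This stands; they are matters to confirm.
- **Discretion and detection.** The eligibility criteria are short and mostly factual, and VF and non-VF are tested separately. The state registries (Data Collection) cover all attended arrests, so selective non-enrolment could be examined afterwards. At 2-5% survival, a crew would have to recognise a rare future survivor during CPR, so shifting four to six survivors would probably mean misallocating many patients. This stands, and it makes the Fisher figures a measure of fragility only.

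None of this answers the remaining point. A constant block size in print, with local custody by unblinded recruiters, is a stated choice, and past allocations carry information that opacity cannot remove.

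**Conclusion.** The point holds as a modest, conditional weakness that is worth correcting because the correction is simple. Where use is tracked across a station, the next guess is right about 56-60% of the time after one to four envelopes of a block are seen. It averages 65%, with 17% of allocations certain, only if the whole block is followed. For a crew relying on its own vehicle the advantage is slight.

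These figures assume 5:5 blocks, an observer who knows the block size, and envelopes that can be assigned to their block. No evidence of selective enrolment or envelope misuse is claimed. The sample sizes and the intention-to-treat principle are unaffected.

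**What to change.** 1. For envelopes not yet issued, generate the lists within state with randomly varying block sizes and do not disclose the sizes to crews. Certainty about the last envelopes of a block then largely disappears. Some guessing advantage remains for anyone who tracks the imbalance between arms. Avoid relying mainly on small blocks.
2. Have each vehicle use the lower-numbered of its two envelopes first. Strict number order cannot hold across vehicles that carry stock in parallel, so the rule applies within a vehicle.
3. State that every opened envelope counts as a randomisation and is analysed in its assigned arm, in keeping with the stated intention-to-treat analysis.
4. Confirm that envelope number and opening time are logged, and add this to the Patient Care Record if the full protocol does not already require it.

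The cost is slightly looser arm balance within a state, which matters little with more than 1,200 patients in each comparison. The Background describes the trial as being conducted, so undistributed envelope stock would also have to be replaced in the three states, which is more than a change to the list-generation code.
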